#### Assessment of the comparability of the current ferritin assay platforms

Ferritin values assayed using the Abbott ARCHITECT and the Vitros® ortho XT7600 platforms will be compared using a one sample paired *t*-test. Bland-Altman plots and Passing and Bablok regression for comparing two methods will be used to assess agreement, constant disagreement or proportional disagreement of results obtained using the two platforms.

*Health economic analysis* will also be carried out, using the primary outcome measures for the trial to inform a modelling study. We will borrow cost and quality of life estimates from other studies/data sources.

### Methods in analysis to handle protocol non-adherence and any statistical methods to handle missing data {20c}

Both primary and secondary endpoints will be analysed according to the intention-to-treat principles (All participants data will be analysed according to the treatment allocation, regardless of what treatment they received and either they completed the follow-up or not). A secondary per-protocol analysis of all endpoints will be conducted. The per-protocol population will be all those who completed the treatment as allocated in the 2 groups.

Missing data will not be imputed. However, those with missing data will be described. This number is expected to be small (< 5% of randomised patients) and the same in each arm as maintenance haemodialysis patients attend haemodialysis three times per week, almost no First Nations dialysis patients leave the Northern Territory, and we will follow patients who move back to their community.

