### Intervention description {11a}

#### Treatment of study participants

Participants are randomised to either Arm A: Intervention IV Iron treatment group (Figs. 1 and 2), or Arm B: Control group receiving no intravenous iron treatment (Figs. 1 and 2). After the randomisation, participants receive monthly treatment as per their randomisation of either monthly intravenous iron if serum ferritin ≥ 700 μg/L and ≤ 2000 μg/L and TSAT < 40% (Arm A) or no IV iron treatment (Arm B) for up to 36 months. Study treatment is withheld if monthly testing demonstrated ferritin > 2000 μg/L and/or TSAT ≥ 40%. These markers will be measured prior to administration of Arm A or B treatment. For both Arms A and B, if the serum ferritin level is < 700 μg/L and TSAT < 40%, rescue therapy is administered. All treatment is administered during dialysis via the ports on the dialysis circuits (see additional file 2).

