#### Intervention treatment Arm A and the control Arm B

Intravenous iron polymaltose is administered according to the standard clinical protocol during haemodialysis. For Arm A, patients receive IV iron polymaltose 200 mg during each of the first 2 haemodialysis sessions at the start of the study, and during each of the first 2 dialysis sessions of the week following the monthly blood tests for all subsequent months (i.e. 400 mg per month). If monthly testing demonstrates ferritin > 2000 μg/L and/or TSAT ≥ 40%, IV iron is withheld for the month. The IV iron is restarted as per protocol when the monthly tests demonstrate ferritin > 700 μg/L and ≤ 2000 μg/L and TSAT < 40%. Rescue therapy of 400 mg of iron polymaltose is administered intravenously on haemodialysis if ferritin ≤ 700 μg/L and TSAT < 40% or as indicated by the treating nephrologist (see below). If monthly testing demonstrates ferritin > 700 μg/L and ≤ 2000 and TSAT < 40%, patients will continue with their allocated randomised treatment (Fig. 2).

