### Study outcomes {12}

#### The primary outcome

This will be involving an intention-to-treat analysis of the differences between the two study arms in the risk of hospitalisation with all-cause infection or death assessed in a time-to-first event analysis.

The primary outcome will be measured from the time of randomi**s**ation every **3** months to the end of the follow-up period.

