### Plans to promote participant retention and follow-up {18b}

The study team makes regular contact (either by phone or preferably in person on the units) with the participants’ treating teams at 3 months and every 6 months. The purpose of this contact is to check compliance with the protocol in terms of study drug prescribing and ordering of routine clinical blood tests. Data is collected and entered into the corresponding visit CRF. Standard operating procedures (SOPs) will contain step by step details on how to recruit patients, collect data and monitor progress.

Participants have the right to choose to withdraw from the study at any time and the investigator may discontinue a participant from the study or from treatment if deemed appropriate at any time. This will have no impact on their normal dialysis and other treatment or care. Reasons why a participant may be withdrawn from the study include, but are not limited to, participant request, primary treating clinician’s request, participant was enrolled and is ineligible (either arising during the study or was overlooked at time of screening and enrolment). Participants will not be withdrawn due to adverse events. The decision to withdraw a participant from the study must be discussed with the coordinating investigators.

If the participant withdraws consent from participating in the study and also withdraws consent for collection of future information, no further evaluations will be performed, and no additional data will be collected. The sponsors may retain and continue to use any data or samples collected before such withdrawal of consent. Participants that are lost to follow-up will continue to be followed by collecting as much data as possible, if possible, until the end of the trial to avoid missing data. Participants withdrawn from the treatment by the treating clinicians will continue to be followed up to the end of the trial to avoid missing data and will be used in the intention-to-treat analysis. This study has allowed for 5% of participant drop-out. Withdrawn participants will not be replaced.

If a participant is withdrawn, the reason is recorded in REDCap.

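### The per-protocol set is defined by completing treatment, so on its plain wording it excludes participants who die on treatment, although death is an endpoint

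*Protocol article*

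**What the plan says.** The section on non-adherence and missing data {20c} makes intention-to-treat the main analysis and adds: "A secondary per-protocol analysis of all endpoints will be conducted". The population follows: "The per-protocol population will be all those who completed the treatment as allocated in the 2 groups". The section gives no list of deviations, no censoring at deviation and no statement on participants who die.

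Other sections show what there is to complete:

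- The primary outcome is the "risk of hospitalisation with all-cause infection or death assessed in a time-to-first event analysis". All-cause death is also a secondary time-to-event outcome.
- Participants receive monthly iron (Arm A) "or no IV iron treatment (Arm B) for up to 36 months". Arm A iron is given "during each of the first 2 dialysis sessions of the week following the monthly blood tests for all subsequent months (i.e. 400 mg per month").
- Arm B is the "Control group receiving no intravenous iron treatment".
- Rescue iron is directed in both arms below a ferritin threshold, and may also be given "or as indicated by the treating nephrologist". Study treatment is withheld above set ferritin or TSAT limits.
- Clinicians may stop treatment. Under {18b}, "Participants withdrawn from the treatment by the treating clinicians will continue to be followed up to the end of the trial", and their data stay in the intention-to-treat analysis. The same section says that adverse events are not grounds for withdrawal.

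**The concern.** Membership of the set depends on something that happens after randomisation and that an endpoint event can prevent. Death is the clear case: it is a component of the primary outcome, a secondary outcome and a safety outcome, and it ends treatment. A set limited to completers therefore removes fatal events because they are events.

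A second route is possible but not certain. Only Arm A has a study drug that can be stopped. The trial is open-label, and the background notes that IV iron has been linked to infections in some studies, so a clinician might stop iron after an infection admission. That would turn an Arm A primary event into a non-completer. Arm B has a route of its own: iron given at the nephrologist's discretion could be read as departing from an allocation of no iron.

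The trial asks whether iron is safe with respect to infection and death. A planned analysis that discards deaths is a poor check on that question, and if exclusions differ by arm it can mislead in either direction.

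**Working it through.** **What needs no assumed figure.** Set the definition beside the endpoints. If a participant who dies during the treatment period has not completed treatment, the per-protocol set contains no on-treatment deaths. The per-protocol all-cause death analysis then has none to count, and the composite reduces to infection admissions among survivors.

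**Inputs for the size of any bias**

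- Two-year risk of the composite: 60% (Sample size {14}). As a check on that section, two proportions of 60% and 48% at 80% power need 270 per arm, and 540/0.95 = 569 after 5% dropout, close to the stated 576. That figure is not in dispute.
- Share of first events that are fatal: d = 25%, **assumed** (range 15% to 30%).
- Share of participants with a non-fatal event who are excluded as non-completers: f, **assumed**, set separately by arm.
- True HR: 1.00.

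**Formula.** Fatal first events are dropped in both arms. At two years the kept fraction of an arm is 0.40 event-free plus 0.60(1 − d)(1 − f) with a non-fatal event. The apparent risk is

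r(f) = 0.60(1 − d)(1 − f) / [0.40 + 0.60(1 − d)(1 − f)],

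and the approximate HR is ln(1 − r_A)/ln(1 − r_B).

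**Results with d = 25%**

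- f = 0: r = 0.45/0.85 = 0.529, ln(1 − r) = −0.754
- f = 10%: r = 0.405/0.805 = 0.503, ln(1 − r) = −0.699
- f = 20%: r = 0.36/0.76 = 0.474, ln(1 − r) = −0.642

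| Excluded non-fatal events, Arm A / Arm B | HR by formula | HR by Cox model on simulated data |
|---|---|---|
| 0% / 0% (deaths only, both arms) | 1.00 | 1.00 |
| 10% / 0% | 0.699/0.754 = 0.93 | 0.93 |
| 20% / 0% | 0.642/0.754 = 0.85 | 0.85 to 0.86 |
| 30% / 0% | 0.77 | 0.78 |
| 50% / 0% | 0.59 | 0.60 |
| 10% / 10% or 20% / 20% | 1.00 | 1.00 |
| 10% / 20% | 0.699/0.642 = 1.09 | 1.08 |

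The simulation used exponential event times truncated at two years. Moving d between 15% and 30% changes these values by about 0.01.

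**Loss of data when deaths alone are dropped.** With d = 25%, fatal first events are 0.60 × 0.25 = 15% of participants, about 86 of 576. A model that also lets people die after an infection admission loses 13% to 24% of participants by two years for d between 15% and 30%, with a null HR of 0.99 to 1.00. In that model, adding Arm A-only exclusion of 10% to 20% of infection admissions gives HRs of 0.94 to 0.85, and a nominal 5% test would reject in 8% to 22% of trials of 576.

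**The case against.** **The literal reading is implausible.** Recruitment runs from 16 December 2020 to about 30 June 2023 and the project ends with 2023, so almost nobody could complete 36 months. The authors may mean treated as allocated while under follow-up, which would keep participants who die on allocated treatment. That is a sensible definition, but it is not the one written. If completion means reaching the end of the participant's own planned treatment period, however short, death still prevents it.

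**The protocol has no rule that stops iron for infection.** This stands. Active infection and raised CRP restrict entry only, withholding depends on ferritin and TSAT, and adverse events are not grounds for withdrawal. Clinician discontinuation is possible, but its rate and any link to infection are not given.

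**A bias in favour of iron does not follow.** A reader might infer that nearly everyone in Arm B completes, that exclusions fall mainly on Arm A, and that the analysis would therefore tend to show iron as protective. The documents do not support this. Every HR below 1.00 in the table comes from an assumed exclusion rate confined to Arm A. Arm B participants can also be excluded, and if that happens more often after events the bias reverses.

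**Withholding and rescue are part of the regimen.** Largely right: the text has participants resume allocated treatment afterwards, so counting either as non-adherence would be strained. Only iron given at the nephrologist's discretion is unclear.

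**Details belong in the analysis plan.** A deviation list commonly does. But the protocol does not leave the population open: it states a definition, and that definition depends on the outcome.

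**Conclusion.** The point holds as a defect in a stated definition. On its plain wording, the per-protocol set excludes participants who die on treatment and is applied to endpoints that include death. That part rests on the text alone.

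The effect on the treatment comparison cannot be fixed from the document. It is nil (HR near 1.00) if deaths drop out of both arms alike and nothing else differs. It is about 0.93 to 0.85 if 10% to 20% of Arm A participants with non-fatal events are also excluded, and about 1.08 if the exclusions are 10% in Arm A and 20% in Arm B. All of these assume 25% of first events fatal and exponential times with a 60% two-year risk.

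The analysis is secondary. The intention-to-treat primary result, the sample size and the interim stopping rule do not depend on it. The definition should be changed, but the trial's main conclusion is not at risk.

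**What to change.** Replace the completer definition with an on-protocol analysis that:

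- keeps every eligible randomised participant from day 1
- counts death on allocated treatment as an event, not as non-completion
- counts protocol-directed withholding and rescue as adherent in both arms
- lists in advance, without reference to outcome, what is a deviation, and says how iron given at the nephrologist's discretion is classed
- censors at the first listed deviation and counts all events before it.

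Censoring at deviation may itself be informative. Inverse-probability-of-censoring weights built from the monthly blood results already collected (haemoglobin, ferritin, TSAT, CRP) and from admissions would address this. They are an optional addition.

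The cost is a change of wording and modest programming to derive deviation dates from existing dosing records. No new data, participants or visits are needed.

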### Plans to give access to the full protocol, participant-level data, and statistical code {31c}

This protocol paper provides the full study protocol. Readers can contact the authors if they are interested in any other data or documentation of the study.

## Oversight and monitoring

### Composition of the coordinating centre and trial steering committee {5d}

#### Trial coordination teams

This trial is coordinated from the Menzies School of Health Research in Darwin, but a coordination team is also set up in Alice Springs. The teams coordinate the day to day running of the trial and meet weekly and work in collaboration with all the other investigators and research staff.

In both Alice springs and in Darwin, the team consist of:
Clinical Trial manger and the Operational research support managerThe principal investigators of the two centresTwo other chief investigators of the studyAll the research nurses and Aboriginal research assistantsOther members of the research investigator teams are invited to the meetings when needed

#### Trial management committee (TMC)

The trial management committee includes a chair, co-chair, all chief investigators and associate investigators, the clinical trial manager, research staff and chairs or proxy of each FNRG. This committee is the steering committee of the trial responsible for all aspects of the trial and making sure the trial is on course and meets every 2 months. A number of out session discussion also occur when needed.

### Composition of the data monitoring committee, its role and reporting structure {21a}

#### Data safety and monitoring board (DSMB)

An independent DSMB (none of whom are chief investigators or associate investigators) has been established to review the progress of the study and monitor adherence to the protocol, participant recruitment, outcomes, complications and other issues related to participant safety. They also monitor the assumptions underlying sample size calculations for the study and alert the investigators if they see substantial departures from the assumptions as the data accumulate.

The DSMB includes two clinician-researchers familiar with clinical trials, a statistician, and a First Nations clinical researcher. The DSMB met before recruitment commenced and 6 months following commencement of recruitment and will continue to meet at annual intervals and at its conclusion. Progress reports documenting serious adverse events will be provided to the DSMB 6-monthly. We have planned a formal interim analysis.

The DSMB will make recommendations as to whether the study should continue or be terminated and consider participant safety or other circumstances as grounds for early termination, including either compelling internal or external evidence of treatment differences or feasibility of addressing the study hypotheses (e.g. poor participant enrolment, poor adherence).

#### First Nation (Aboriginal and Torres Strait Islander) Reference Groups (FNRG)

Two First Nation Reference Groups (FNRG) have been established to provide oversight regarding culturally appropriate conduct of the research in their respective HREC-approved jurisdictions. Each FNRG consists of 7–10 members, of whom all are First Nations. One member each is an independent First Nations academic, with two [2] members from each of the dialysis units: FNRG [1] Top End – Royal Darwin Hospital, Nightcliff, Palmerston, Katherine and Tiwi Islands. FRRG [2] Central Australia - Alice Springs Hospital, Flynn Drive, Gap Road and Tenant Creek.

Of the two members from each site, ideally one will be male, and one will be female. The members can self-nominate or be nominated by or from First Nations communities and community-controlled services which are partners in this study. The FNRG will meet regularly throughout the period of the research conduct, and a representative will join the Trial Management Committee. If requested by the FNRG, the INFERR Clinical Trial Manager or the principal or chief investigator will attend the meetings to provide study progress reports.

### Adverse events reporting and harms {22}

#### Serious adverse events (SAEs)

A SAE is defined as any experience that:
Results in deathIs life threatening.
The term “life threatening” refers to an event in which the participant was at risk of death at the time of the event. It does not refer to an event which hypothetically may have caused death if it were more serious.Results in unexpected prolongation of existing hospitalisationResults in persistent or significant disability/incapacityIs a medically important event or reaction.

All SAEs that are considered related to the study drugs require reporting on the SAE form. If the SAE is attributable to disease progression, then this does not require expedited reporting in this trial, even when death is the outcome. The site PI is required to report any SAEs that occur at their site to the approving ethics committee in accordance with local guidelines; in addition, the site PI must adhere to any local institutional reporting requirements and study sponsor. Safety reporting will be in line with the National Health and Medical Research Council’s (NHMRC) Guidance: Safety monitoring and reporting in clinical trials involving therapeutic goods (2016) [53].

#### Suspected unexpected serious adverse reactions (SUSAR)

An adverse event that is both serious and unexpected (not listed in the product information and not attributable to disease progression) and related to the study drug meets the definition of a SUSAR. All SUSARs must be entered on the SAE CRF and reported to the sponsor or delegate within 24 h from the time of the site study team becoming aware of it. If the SUSAR is fatal or life threatening, the Sponsor will report to the TGA within 7 calendar days of becoming aware and any follow-up reports required within a further 8 calendar days, and for all others 15 calendar days of becoming aware.

The site PI is required to report any SUSARs that occur at their site to the approving ethics committee in accordance with local guidelines; in addition, the site PI must adhere to any local institutional reporting requirements. Safety reporting will be in line with the NHMRC’s Guidance: Safety monitoring and reporting in clinical trials involving therapeutic goods (2016) [53].

#### Adverse drug reactions (ADRs)

Investigators will be asked to report all suspected adverse drug reactions (regardless of severity or seriousness) which are thought to be related to study drugs in both intervention and control arms within the first 24 h post study drug infusion. These data will be collected routinely on CRFs.

#### Causality

##### Assessment of causality for study drugs

The principal investigator or their delegate is responsible for assessing the relationship to study drugs using clinical judgement and the following considerations:
*Unrelated*: Evidence exists that the adverse event has an aetiology other than the study drugs. For SAEs, an alternative causality must be provided (e.g. pre-existing condition, underlying disease, intercurrent illness or concomitant medication).*Related*: There is reasonable possibility that the event may have been caused by the study drugs. It should be emphasised that ineffective treatment should not be considered as causally related in the context of adverse event reporting.

The degree of certainty with which an adverse event is attributable to treatment, or an alternative cause will be determined by how well the event can be understood in terms of:
Temporal relationship with the administration of the treatment or cessation of treatmentReactions of a similar nature previously observed in the individual or others following treatment.

The relationship of the adverse event to treatment will be specified as follows:
*Not related*In the PI’s opinion, there is not a causal relationship.*Unlikely*The temporal association between treatment and the adverse event is such that treatment is not likely to have any reasonable association.*Possibly*The adverse event could have been caused by treatment.*Probably*The adverse event follows a temporal sequence from the time of treatment and cannot be reasonably explained by the known characteristics of the participant’s clinical presentation/history.*Definitely*The adverse event follows a reasonable temporal sequence from the time of treatment or reappears when the treatment is repeated.

##### Non-expedited reporting of adverse events and adverse drug reactions

In addition to the expedited reporting described above, a summary of all adverse drug reactions (to any of the study drugs including SAEs) will be reported to the DSMB and HREC as per local guidelines.

##### Summary of expedited reporting of adverse events and adverse drug reactions

In summary, SAEs *not* thought to be related to the study drug do not need to be reported in this trial; however, this data will be collected for outcome measures. SAEs thought to be possibly, probably or definitely related to study drug (e.g. an anaphylactic reaction to IV iron) must be reported by the PI or CI, research nurse or their delegate to the sponsor (in this case the Clinical Trial Manager and CIs at Menzies) within 24 h of becoming aware of the event. Reporting to the HREC will be in accordance with local guidelines. If it is an expected side effect (i.e. one listed in the product information, such as allergic reaction or diarrhoea), it does not need to be reported to the TGA. If it is both *unexpected* and serious, it needs to be reported to the TGA within 7 days (fatal or life threatening) or 15 days (other).

